### Analysis of secondary outcomes

The secondary outcomes of the FAS and PPS will be analyzed, including the recovery time of clinical symptoms, SARS-CoV-2 nucleic acid testing negative conversion time and negative conversion rate, hospitalization time, antipyretic time, the conversion rate of turning to severe patients, disappearance time of single symptoms, and disappearance rate. All secondary outcomes will be compared between and within groups based on the distribution and changes at baseline and each visit point (Table 4).

**Table 4 T4:** Analysis of secondary outcomes.

	Full analysis set				Per Protocol set			
Variables	SHHS group (n=xx)	LHQW Group (n=xx)	Mean difference 95%CI	*P-Value*	SHHS group (n=xx)	LHQW Group (n=xx)	Mean difference 95%CI	*P-Value*
Time to clinical symptom recovery^a^	xx (xx)	xx (xx)	xx(xx to xx)	.xx	xx (xx)	xx (xx)	xx(xx to xx)	.xx
Time to single symptom recovery^a^								
Fever^a^	xx (xx)	xx (xx)	xx(xx to xx)	.xx	xx (xx)	xx (xx)	xx(xx to xx)	.xx
Cough^a^	xx (xx)	xx (xx)	xx(xx to xx)	.xx	xx (xx)	xx (xx)	xx(xx to xx)	.xx
Fatigue^a^	xx (xx)	xx (xx)	xx(xx to xx)	.xx	xx (xx)	xx (xx)	xx(xx to xx)	.xx
Diarrhea^a^	xx (xx)	xx (xx)	xx(xx to xx)	.xx	xx (xx)	xx (xx)	xx(xx to xx)	.xx
Shortness of breath^a^	xx (xx)	xx (xx)	xx(xx to xx)	.xx	xx (xx)	xx (xx)	xx(xx to xx)	.xx
Sore throat^a^	xx (xx)	xx (xx)	xx(xx to xx)	.xx	xx (xx)	xx (xx)	xx(xx to xx)	.xx
Nausea^a^	xx (xx)	xx (xx)	xx(xx to xx)	.xx	xx (xx)	xx (xx)	xx(xx to xx)	.xx
Vomiting^a^	xx (xx)	xx (xx)	xx(xx to xx)	.xx	xx (xx)	xx (xx)	xx(xx to xx)	.xx
Taste and smell dysfunction^a^	xx (xx)	xx (xx)	xx(xx to xx)	.xx	xx (xx)	xx (xx)	xx(xx to xx)	.xx
Loss of appetite^a^	xx (xx)	xx (xx)	xx(xx to xx)	.xx	xx (xx)	xx (xx)	xx(xx to xx)	.xx
···	···	···	···	···	···	···	···	···
Rate of single symptom recovery^b^								
Fever^b^	xx (xx%)	xx (xx%)	xx(xx to xx)	.xx	xx (xx%)	xx (xx%)	xx(xx to xx)	.xx
Cough^b^	xx (xx%)	xx (xx%)	xx(xx to xx)	.xx	xx (xx%)	xx (xx%)	xx(xx to xx)	.xx
Fatigue^b^	xx (xx%)	xx (xx%)	xx(xx to xx)	.xx	xx (xx%)	xx (xx%)	xx(xx to xx)	.xx
Diarrhea^b^	xx (xx%)	xx (xx%)	xx(xx to xx)	.xx	xx (xx%)	xx (xx%)	xx(xx to xx)	.xx
Shortness of breath^b^	xx (xx%)	xx (xx%)	xx(xx to xx)	.xx	xx (xx%)	xx (xx%)	xx(xx to xx)	.xx
Sore throat^b^	xx (xx%)	xx (xx%)	xx(xx to xx)	.xx	xx (xx%)	xx (xx%)	xx(xx to xx)	.xx
Nausea^b^	xx (xx%)	xx (xx%)	xx(xx to xx)	.xx	xx (xx%)	xx (xx%)	xx(xx to xx)	.xx
Vomiting^b^	xx (xx%)	xx (xx%)	xx(xx to xx)	.xx	xx (xx%)	xx (xx%)	xx(xx to xx)	.xx
Taste and smell dysfunction^b^	xx (xx%)	xx (xx%)	xx(xx to xx)	.xx	xx (xx%)	xx (xx%)	xx(xx to xx)	.xx
Loss of appetite^b^	xx (xx%)	xx (xx%)	xx(xx to xx)	.xx	xx (xx%)	xx (xx%)	xx(xx to xx)	.xx
···	···	···	···	···	···	···	···	···
Time to negative conversion of SARS-CoV-2 PCR testing^a^	xx (xx)	xx (xx)	xx(xx to xx)	.xx	xx (xx)	xx (xx)	xx(xx to xx)	.xx
Rate of negative conversion of SARS-CoV-2 PCR testing^b^	xx (xx%)	xx (xx%)	xx(xx to xx)	.xx	xx (xx%)	xx (xx%)	xx(xx to xx)	.xx
Rate of conversion of severe patients^b^	xx (xx%)	xx (xx%)	xx(xx to xx)	.xx	xx (xx%)	xx (xx%)	xx(xx to xx)	.xx
Antipyretic time^a^	xx (xx)	xx (xx)	xx(xx to xx)	.xx	xx (xx)	xx (xx)	xx(xx to xx)	.xx
hospitalization time^a^	xx (xx)	xx (xx)	xx(xx to xx)	.xx	xx (xx)	xx (xx)	xx(xx to xx)	.xx

a Number, mean, standard deviation;

b Number, percentage.

Continuous data will be summarized using number, mean, standard deviation, minimum, maximum, median, upper and lower quartile. A t-test or Wilcoxon rank test will be applied to compare groups. ANCOVA will be considered to evaluate the influence of covariates. Chi-square test or Fisher exact test will be used to compare groups for categorical data. CMH-Chisquare test and logistic regression will be considered to explore the influence of covariates. Time-to-event data will be estimated by Kaplan-Meier method to compute the median and corresponding 95%CI. Log-rank test will be used for between-group comparison.

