### Inclusion criteria

Diagnostic criteria for COVID-19 are based on the Protocol for the Diagnosis and Treatment of Novel Coronavirus Disease 2019 (9th edition) released by the NHC of the People's Republic of China (General Office Of The National Health And Health Commission, 2022) and include individuals who qualified for eligibility meeting the following criteria: 1) clinically confirmed patients of COVID-19 according to the Protocol for Diagnosis and Treatment of Novel Coronavirus Pneumonia (9th edition) with laboratory confirmed SARS-CoV-2 infection as determined by RT-PCR; 2) patients judged to have mild or moderate COVID-19. (Patients with mild COVID-19 usually present with mild clinical symptoms, without radiological manifestations of pneumonia, whereas patients with moderate COVID-19 patients have a fever and respiratory symptoms, as well as radiological features of pneumonia); 3) presence of one or more symptoms of fever, cough, sore throat, and fatigue when entering the group; 4) the time of admission is not more than 24 hours; 5) patients of either sex who are 18 years or older, and 6) providing written informed consent before enrolling in the trial.

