### Sample size

The study hypothesis is SHHS group will be non-inferior to LHQW group. Clinicians and statisticians set the non-inferiority threshold at 10% and predicted that the recovery rate of clinical symptoms after 7 days of LHQW is about 87% and that of SHHS is 90% according to the literature reports on similar drugs. It is estimated that 94 patients for each group, ie. a total of 188 patients are needed to achieve the power of 80% at a one-sided statistically significant level of 0.025. Considering the possible dropout rate of 20%, 240 patients will be enrolled, that is 120 patients for each group.

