## Statistical analysis plan

### Statistical methods

The statistical analysis plan will comply with the guidelines for the content of statistical analysis plans in clinical trials (Gamble et al., 2017). (**Additional File 3**). After finishing the trial, all statistical analysis tests will be conducted using SAS (version 9.4; SAS Inc., Cary, NC, USA) and one-sided tests with a nominal alpha level of 0.025. All confidence intervals (Cls) will be stated at the 95 confidence level. To assess non-inferiority, the CI lower limit of the difference between groups will be compared with a predefined non-inferiority limit. Non-inferiority could only be declared when the 95% CI lower limit of the difference between groups is not larger than the non-inferiority threshold of 10%.

Continuous outcomes will be described by calculating the mean, standard deviation, median, and minimum and maximum values. The means and standard deviations are reported for normal continuous data. For non-normally distributed continuous variables, the median and interquartile ranges are given. The frequency and proportion of each category are displayed as counting indications.

Between-group comparisons are performed using an independent two-sample t-test (normality, homogeneity of variance) or the Wilcoxon rank-sum test (non-normality, heterogeneity of variance). The paired t-test is used for comparisons within normally distributed groups, and the paired rank-sum test is used for comparisons within non-normally distributed groups. For count metrics, the χ^2^ test or Fisher's exact probability will be required, whereas, for categorical variables, the Wilcoxon rank-sum test will be utilized. Repeated measured outcomes are applied to a generalized linear mixed model analysis.

In patients where baseline indicators are unbalanced, an adjustment to the efficacy contrast of variables such as age, sex, and concurrent therapy is required. The covariance approach is employed for continuous variables, and for count or rank data, logistic regression analysis is performed.

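### Within-arm tests against baseline are planned for all secondary outcomes: for PCR status and common symptoms they measure the course of the illness, not SHHS against LHQW, and for the five time outcomes they are undefined

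*Protocol article*

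**What the plan says.** The trial's question is a comparison of two arms. Sample size states: "The study hypothesis is SHHS group will be non-inferior to LHQW group".

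Analysis of secondary outcomes lists eight endpoints. Five are times: symptom recovery, PCR negative conversion, hospitalization, antipyretic time and single-symptom disappearance. Three are rates: PCR negative conversion, conversion to severe disease and single-symptom disappearance. The section then says: "All secondary outcomes will be compared between and within groups based on the distribution and changes at baseline and each visit point".

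Statistical methods names the within-group tests: "The paired t-test is used for comparisons within normally distributed groups, and the paired rank-sum test is used for comparisons within non-normally distributed groups". All testing is to use "one-sided tests with a nominal alpha level of 0.025".

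On baseline status, Inclusion criteria require "presence of one or more symptoms of fever, cough, sore throat, and fatigue when entering the group" and "laboratory confirmed SARS-CoV-2 infection as determined by RT-PCR".

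The same plan also provides between-group methods for these endpoints: t or Wilcoxon tests, chi-square or Fisher tests, log-rank tests, and a mixed model for repeated measures. Table 4, which the quoted sentence cites, has columns only for the difference between arms with its 95% CI and P value.

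**The concern.** A paired test within one arm has the null hypothesis of no change since baseline in that arm. Patients are selected because they are PCR positive and symptomatic, and the illness is acute. Movement away from baseline is expected whatever they are given. The test therefore picks up natural course plus concomitant care and cannot separate out the contribution of SHHS. The trial has no untreated arm that would show the natural course.

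What is at stake is a set of within-arm P values that could be read as evidence that SHHS works. A second risk is informal comparison of significance across arms: a significant result in one arm and not in the other is not a test of the difference between them.

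There is also a question of feasibility. The sentence covers all secondary outcomes at baseline and at each visit, but a duration such as time to recovery or length of stay has no baseline value to pair with.

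**Working it through.** **Inputs from the article.** One-sided alpha 0.025 (Statistical methods). 120 enrolled and 94 evaluable patients per arm (Sample size). All patients PCR positive with at least one of four symptoms at entry (Inclusion criteria).

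**Assumption.** The natural recovery rate by the time of comparison is not given. It is varied from 5% to 50%.

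**The plan's own figure.** The article states no operating characteristic for the within-arm tests. Its sample size, which supplies the 94, reproduces. With rates 0.87 and 0.90 and margin 0.10:

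- variance = 0.87 × 0.13 + 0.90 × 0.10 = 0.2031
- n = 0.2031 × (1.96 + 0.842)² / 0.13² = 94.3 per arm (stated: 94)

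**Step 1: which outcomes allow a paired test.**

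- Five times: no baseline value and no value at each visit, so no pair exists and the test is undefined.
- PCR and single-symptom rates: the underlying status (positive or negative, present or absent) exists at baseline and at each visit, so a paired comparison can be formed.
- Conversion to severe: nobody is severe at entry, so the only possible change is worsening. With 120 patients, significance for worsening occurs in 0.1% of trials at a 1% rate and 3% at a 2% rate. Neither outcome says anything about SHHS against LHQW.

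**Step 2: threshold where the test can be formed.** Among patients who have the condition at baseline, change can only go towards recovery. With k recoveries and no reversals, the exact one-sided paired P is 0.5^k.

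- k = 5: 0.5^5 = 0.0313, above 0.025
- k = 6: 0.5^6 = 0.0156, below 0.025

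Six recoveries are enough. The exact sign test is a stand-in, because the article names only the paired t and paired rank-sum tests. For yes/no data that all change one way, the exact signed-rank test reduces to it. The paired t-test needs even fewer: 4 recoveries of 120 give t = √(119 × 4/116) = 2.03, above the critical value of 1.98.

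**Step 3: chance of a significant within-arm result with an inert product.** This is P(X ≥ 6) for X ~ Binomial(n, r), where n is the number in the arm with the condition at baseline and r is the assumed natural recovery rate.

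| n | r = 5% | r = 10% | r = 20% | r = 30% | r = 50% |
|---|---|---|---|---|---|
| 120 | 56% | 98% | >99.9% | >99.9% | >99.9% |
| 94 | 33% | 92% | >99.9% | >99.9% | >99.9% |
| 60 | 8% | 56% | 99% | >99.9% | >99.9% |
| 30 | 0.3% | 7% | 57% | 92% | >99.9% |
| 10 | <0.1% | <0.1% | 0.6% | 5% | 38% |
| 5 | never | never | never | never | never |

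The rows for 94 and 120 apply to PCR status, since every patient is positive at entry. For a single symptom, n is the number who have it, which is not known in advance.

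**Step 4: the between-group test under the same conditions.** In 20,000 simulated trials per setting, with identical recovery in both arms and 94 or 120 patients per arm, the one-sided between-group test rejected in about 2% to 3%, close to its nominal 2.5%.

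**The case against.** The strongest reply is that the inference that matters is already between-group. The non-inferiority rule uses the confidence interval for the difference between arms. Table 4 has no within-group column. No passage rests a claim on a within-arm P value, and the Discussion makes its efficacy statement conditional on the non-inferiority conclusion. All of this stands and limits the impact. It does not rescue the sentence, which orders comparisons that its own cited table has no place for.

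Three stronger readings are tempting, and the documents do not support them.

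- A reader might infer that every secondary outcome would be significant in nearly every trial of an inert product. That can hold only for the PCR rate and for symptoms common at baseline. It cannot hold for the five time outcomes or for severe conversion. Entry requires only one of four symptoms, and Table 4 includes symptoms that are not entry criteria, such as diarrhea and vomiting, so some rows may have few affected patients.
- A reader might take the 87% recovery rate in Sample size as the natural rate and quote a vanishingly small P value. That figure is the assumed rate on LHQW for the primary outcome, so it is neither natural recovery nor a secondary endpoint.
- A reader might conclude that the paired-test sentence has to go altogether. It is a general methods statement, and vital signs are also recorded at baseline and daily. Only its use for efficacy outcomes is at issue.

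**Conclusion.** The point holds in limited form, and its severity is minor. The plan states a within-arm comparison for all secondary outcomes. That comparison is undefined for five of the eight and uninformative for severe conversion. For PCR status and common symptoms it measures change over the illness and not the treatment contrast.

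For PCR status, where all patients count, an inert product would produce a significant within-arm result in 33% to 56% of trials at 5% natural recovery, 92% to 98% at 10%, and over 99.9% at 20% or more (94 and 120 patients respectively). For a symptom present in 30 patients the figure is 57% at 20% recovery.

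These figures rest on an assumed recovery rate, on the sign test as stand-in, and on analysing only patients who have the condition at baseline. The primary non-inferiority decision, the sample size and the contrasts in Table 4 are not affected. Only the secondary within-arm P values are.

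**What to change.** - In Analysis of secondary outcomes, remove the within-group part of the quoted sentence, so that secondary outcomes are compared between groups only.
- In Statistical methods, add that paired tests are not used for efficacy outcomes and that change from baseline by arm is reported descriptively.
- Base secondary inference on what is already planned: between-group differences with 95% CI, log-rank tests for the time outcomes, and the mixed model for repeated measures, read through its treatment and treatment-by-visit terms.

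The cost is a change of wording and fewer tests to run. No data or patients are lost, and Table 4 can stay as it is.

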### Secondary outcomes

The secondary outcomes are the recovery time of patients self-reported clinical symptoms, SARS-CoV-2 nucleic acid testing negative conversion time, and negative conversion rate, hospitalization time, antipyretic time, the incidence of severe patients, single symptom disappearance time, and disappearance rate.

Criteria for judging the curative effect:(1) Recovery time and cure rate of clinical symptoms: The recovery of clinical symptoms refers to the disappearance of the main symptoms, ie. fever, coughing, sore throat, and fatigue. The cure rate is defined as the proportion of patients whose clinical symptoms recovered after the end of treatment on the seventh day.(2) SARS-CoV-2 nucleic acid testing negative conversion time and negative conversion rate: Taking the first time of the two consecutive respiratory tract SARS-CoV-2 PCR negative tests (sampling interval at least 1 d) as the SARS-CoV-2 PCR testing negative time (the SARS-CoV-2 nucleic acid testing negative conversion time equals the SARS-CoV-2 PCR testing negative time–the diagnosis time of the patient).(3) Hospitalization time: the time from patient admission to discharge. The discharge standard refers to the release from isolation or discharge criterion of the protocol for diagnosing and treating novel coronavirus pneumonia (9th edition).(4) Antipyretic time: The body temperature is less than 37.4°C after treatment, for 24 h or more.(5) The conversion rate of turning to severe patients: the proportion of patients who develop severe infection 7 days after taking medicine.

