### Imputation of missing data

Missing values of the primary and secondary outcomes will be carried forward from the latest observation data to the final results (LOCF method).

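### Table 4 reports the time outcomes as mean (SD) and mean difference, while the text below it specifies Kaplan-Meier and log-rank; the plan does not say how patients without the event enter a mean

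*Protocol article*

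**What the plan says.** All references are to the protocol article.

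- **Analysis of secondary outcomes, Table 4.** The rows for time to clinical symptom recovery, time to each single symptom's recovery, "Time to negative conversion of SARS-CoV-2 PCR testing^a", antipyretic time and hospitalization time all carry footnote a, which reads "a Number, mean, standard deviation". Rate rows carry footnote b (number, percentage). The effect column is "Mean difference 95%CI", for both the full analysis set and the per-protocol set.
- **Same section, text below Table 4.** "Time-to-event data will be estimated by Kaplan-Meier method to compute the median and corresponding 95%CI". "Log-rank test will be used for between-group comparison". For continuous data the same paragraph says "A t-test or Wilcoxon rank test will be applied to compare groups". It does not say which rule governs which row.
- **Imputation of missing data.** "Missing values of the primary and secondary outcomes will be carried forward" from the latest observation. Time outcomes are not exempted.
- **Table 1.** Symptoms and PCR are assessed daily, with the last column at day 8.
- **Secondary outcomes.** PCR conversion is dated to the first of two consecutive negative tests at least a day apart. Length of stay is defined without a day-8 limit: "Hospitalization time: the time from patient admission to discharge".

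**The concern.** The table and the text give two different analyses for the same rows. A Kaplan-Meier median with a log-rank test accommodates patients who have not had the event by the end of observation. A mean, an SD and a mean difference do not, unless such patients are left out or given a time. Because the text also offers a t-test or a Wilcoxon test for continuous data, the P-value in a time row could come from any of three tests.

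What is at stake is how the secondary time outcomes read. Averaging only patients with the event compares subsets selected by outcome, and it pulls the arms together when fewer patients recover in one of them. In a non-inferiority trial that is the flattering direction.

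**Working it through.** **1. The plan's own figure.** The Sample size section gives the rates used below: 87% recovered at day 7 on LHQW, 90% on SHHS, margin 10%, one-sided 0.025, power 80%, dropout 20%.

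n per group = (1.960 + 0.842)² × (0.87×0.13 + 0.90×0.10) / (0.03 + 0.10)² = 7.849 × 0.2031 / 0.0169 = 94.3.

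The plan states 94 (95 if rounded up). With dropout, 94/0.80 = 117.5, and the plan enrols 120. The figure reproduces, and the point here does not depend on it.

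**2. How many patients have no time.** On those rates, 0.13 × 120 = 15.6 LHQW patients and 0.10 × 120 = 12 SHHS patients are unrecovered at day 7. The dropout allowance is 0.20 × 120 = 24 per arm. For PCR, two consecutive negatives are needed and the last scheduled sample is on day 8, so the latest conversion that the schedule can confirm is day 7.

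**3. What a mean would show.** Assume a constant hazard (the documents give no time distribution) and count from the start of treatment. With p the proportion having the event by day 7:

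- λ = −ln(1−p)/7
- mean among patients with the event = 1/λ − 7(1−p)/p
- restricted mean to day 7 = p/λ

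| p by day 7 | 1/λ | Mean, events only | Restricted mean |
|---|---|---|---|
| 0.90 | 3.040 | 3.040 − 0.778 = 2.262 | 2.736 |
| 0.87 | 3.431 | 3.431 − 1.046 = 2.385 | 2.985 |
| 0.77 | 4.763 | 4.763 − 2.091 = 2.672 | 3.667 |

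Differences in days:

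| Comparison | Events only | Restricted mean | Ratio |
|---|---|---|---|
| 87% v 90% (planned rates) | 0.12 | 0.25 | 0.49 |
| 87% v 77% (deficit equal to the margin) | 0.29 | 0.68 | 0.42 |

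**4. A slower outcome.** The documents give no PCR conversion rates, so this is an assumed range with the same formulas. The plan counts PCR time from diagnosis, so these figures show direction and rough size only.

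| Assumed conversion by day 7 | Events only | Restricted mean |
|---|---|---|
| 40% v 50% | 0.10 | 0.43 |
| 60% v 70% | 0.16 | 0.51 |
| 80% v 87% | 0.21 | 0.49 |

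**5. The other way to form a mean.** If every non-event is set to day 7 and follow-up is complete, the mean is the expected value of the smaller of T and 7. That is the restricted mean: 2.98 at 87% and 3.67 at 77%, with no shrinkage. It fails for early dropouts. If the last observed day were entered as the time, a patient who left unrecovered on day 2 would score 2 days, less than the 2.39-day average of recovered patients at 87%.

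**The case against.** The strongest reply is that the text already names the right method. Kaplan-Meier implies censoring, and the Table 4 column heading looks like a generic placeholder, because it also stands over the rate rows, where a mean difference cannot be meant literally. That stands in part: the heading alone proves little. But the footnotes separate times from rates and assign mean and SD to the times, so the conflict with the text remains.

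Three stronger readings are tempting, and the documents do not support them.

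- **That the table will show only about 40% of the real difference.** This needs events-only means, which the plan never specifies, and a deficit equal to the full margin. At the planned rates the gap is 0.25 − 0.12 = 0.13 days, about 3 hours. Setting non-events to the last day under complete follow-up gives no shrinkage.
- **That LOCF turns censored times into events.** LOCF is stated in the missing-data section, not in Table 4. A patient seen on day 8 still symptomatic or PCR-positive is not missing, and carrying forward a symptom as present leaves a non-event. The problem is that the rule covers all secondary outcomes and has no defined meaning for a time whose event has not occurred.
- **That hospitalization time is cut off at day 8.** Its definition has no such limit, and the end of scheduled visits does not show that later discharge dates go unrecorded.

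It is also fair that detailed censoring rules are usually left to the full analysis plan, which is not shown. The finding is therefore the contradiction in what is printed, not the absence of those rules.

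**Conclusion.** The point holds as a contradiction confined to the secondary time outcomes. Mean (SD) with a mean difference, and a Kaplan-Meier median with a log-rank test, cannot both be the planned report for the same rows. On the plan's own recovery rates, a mean cannot be formed for symptom recovery without an unstated choice about roughly 10 to 13% of patients plus dropouts. The same can be expected for PCR conversion.

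The size depends on that choice. It ranges from no distortion (last day assigned, complete follow-up) to about half of the restricted mean difference lost (events only, planned rates), and more for slower outcomes under the assumed PCR range. These sizes rest on the constant-hazard assumption; the contradiction does not.

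A reader might infer that the non-inferiority conclusion is at risk. It is not: the primary outcome is a day-7 proportion, and neither its analysis nor the sample size uses these rows. The change should be made, but the trial's main conclusion does not hang on it.

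**What to change.** 1. In Table 4, for the symptom-recovery, single-symptom, PCR-conversion and antipyretic time rows, replace mean (SD) and mean difference with number of events, number censored, Kaplan-Meier median (95% CI) and log-rank P. A restricted mean difference to day 7 or 8, or a hazard ratio, with 95% CI is optional if an effect size is wanted.
2. In the text below the table, name these rows as the time-to-event outcomes, so that the t-test/Wilcoxon rule does not compete for them, and state that patients without the event are censored at their last assessment.
3. In the missing-data section, state that LOCF does not apply to time outcomes.
4. Treat hospitalization time this way only where the discharge date is not observed.

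The cost is a table shell and a few sentences. Daily assessment is already scheduled and the text already commits to Kaplan-Meier and log-rank, so no new data are needed.
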